**Secondary objectives:**

1. To evaluate the effect of a FAM-CARE program of HIV care on the proportion of children with viral suppression (undetectable HIV RNA levels) and with HIV RNA >1,000 copies/mL at 6 and 12 months after enrollment into the study.

*Hypothesis: Children in the FAM-CARE program will have improved viral suppression (undetectable RNA) and lower rates of HIV RNA >1000 copies/mL at 6 and 12 months compared to children in control facilities.*

1. Determine the individual and family factors associated with viral suppression and HIV RNA >1,000 copies/mLin children 18 months after enrollment in FAM-CARE and control facilities.
2. To evaluate the effect of a FAM-CARE program of HIV care on loss to follow-up (not seen in clinical care >3 months) and ART initiation in HIV-positive children not on ART at study entry.

*Hypothesis: Children in the FAM-CARE program will have lower rates of loss to follow-up and more children initiated on ART compared to children in control facilities.*

1. Evaluate the acceptability of the FAM-CARE program to caregivers and health care providers.

*Hypothesis: The FAM-CARE program will be acceptable to caregivers and health care providers.*

1. **EXPECTED RESULTS**

The FAM-CARE approach is a way of caring for children and their families within health services which ensures that care is planned around the whole family, not just an individual, and in which all family members are recognized as care recipients. The approach recognizes the vital role that families play in ensuring the health and well-being of infants, children, adolescents, and family members of all ages. It is hypothesized that such a family-centered care program will be successful in enrolling HIV-positive children, their HIV-positive mothers and their partners into continuous follow-up through incentivizing care-seeking within a family and reducing barriers to treatment and retention. Through clinic visits involving all HIV-positive family members, health care provider workload is decreased, as they will not have to see individual members of the family on different days; this also benefits the family by decreasing the amount of times they are required to come to the facility for clinic visits or to pick up ART.

Our study will:

- Assess the effect of the FAM-CARE program on rates of viral suppression and HIV RNA level >1,000 copies/mL in HIV-positive children on ART, and factors associated with these endpoints.

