- Evaluate the effect of the FAM-CARE program on missed visits, time out of care, and loss to follow-up of HIV-positive children (pre-ART and on ART), compared to the current standard of care program, and the association of these outcomes with viral suppression.
- Assess the effect of the FAM-CARE program on ART initiation among HIV-positive children not on ART at study entry.
- Assess the feasibility and acceptability of the FAM-CARE program to caregivers and health care providers.

In the Swaziland family-centered care program, no additional staff is required for the program. By simply reorganizing the way services are provided, without additional costs to the program, the program should provide more efficient and effective services that promote improved retention in care, ART initiation, adherence, and the primary endpoint of viral suppression for children and also their adult family members. Should family-centered care prove to be effective, feasible, and acceptable, the program should be easily transferable to other resource-limited country settings, and contribute to the global UNAIDS/PEPFAR 90-90-90 targets by ensuring viral suppression in children on ART.

1. **RESEARCH DESIGN AND METHODS**

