**Enroll**

**HIV-positive child <15 years**

- **Receiving ART (endoints: viral suppression/HIV RNA >1,000 c/mL; pattern of retention)**
- **Not receiving ART (endoints: ART initiation; viral suppression /HIV RNA >1,000 c/mL; patterns of retention)**

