**Follow-up: 18 months**

Our primary endpoints of viral suppression and HIV RNA >1,000 copies/mL will be evaluated among HIV-positive children entering the study who are initiating or receiving ART. The sample size will be powered to detect a difference in viral suppression/HIV RNA >1,000 copies/mL in children receiving ART in the FAM-CARE sites to those receiving ART in control sites. For HIV-positive children entering the study who are not currently on ART, we will be able to compare retention in care and the proportion of children initiating ART between those enrolled in the FAM-CARE sites to those in control sites.

At FAM-CARE sites, it is estimated that 10-20% of HIV-positive children may not be enrolled in the FAM-CARE program, because of disclosure or other issues within the family. These children will still be enrolled in the prospective cohort as long as there is >1 family member who is also HIV-positive; we will be able to compare suppression/ART failure/retention rates between children in FAM-CARE sites enrolled in the FAM-CARE program and not enrolled in the FAM-CARE program, although the study will not be powered based on this comparison. We will also be able to compare overall rates of viral suppression/HIV RNA >1,000 copies/mL among all children (regardless of actual participation in FAM-CARE programs) seen at facilities with the FAM-CARE program to those in control facilities.

An individual family may have more than one HIV-positive child, and more than one HIV-positive child that is receiving treatment; based on a review of pediatric enrollment at two sites, it is estimated that ~15% of HIV-positive children come from families with more than one child receiving ART. Viral suppression rates in children from families with more than one child on treatment may be correlated, particularly in the FAM-CARE program. We will create a “family identification number” that will be used at both FAM-CARE and control sites to identify children enrolled in the study who come from the same family, which will allow controlling for potential correlation during analysis.

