In both intervention and control facilities, all HIV-positive children under 15 years of age will be enrolled into the study until the number of target “family units” as per sample size calculation is achieved. A “family unit” is defined as a family in which at least one child <15 years enrolled in the study is receiving ART and has at least one additional family member who is HIV-positive. In the majority of instances, a family will have only one HIV-positive child on ART, and the family “unit” equals one enrolled child. However, if a family (in FAM-CARE or control sites) has more than one HIV-positive child on ART, all children on ART are enrolled, but for sample size purposes, this will equal one enrolled “family unit”. Data from all enrolled children will be included in the analysis with adjustment potential correlations due to family units (see analysis plan).

HIV-positive children initiating or receiving ART at study entry will contribute to the endpoints related to viral suppression and HIV RNA >1,000 copies/mL. HIV-positive children who are not receiving ART at study entry will contribute to endpoints related to retention in care and proportion of children not on ART who initiate ART during the study.

Assuming a 20% refusal of entry into FAM-CARE, that 15% of families will have more than one HIV-positive child enrolled in the study, and 15% of children will not be receiving ART at study entry, we estimate we will need to enroll approximately 666 HIV-positive children into the study (333 per arm) to achieve the target sample size of 444 HIV-positive children receiving ART from unique families.

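### The protocol names conflicting populations for the secondary retention/loss-to-follow-up endpoint: children not on ART at entry, all enrolled children, or children on ART

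*Protocol*

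**What the plan says.** Three different populations can be found for the same endpoint.

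- **Children not on ART at entry.** Study sampling procedures divides endpoints by ART status in two consecutive sentences. The first reads "HIV-positive children initiating or receiving ART at study entry will contribute to the endpoints related to viral suppression and HIV RNA >1,000 copies/mL". The second reads "HIV-positive children who are not receiving ART at study entry will contribute to endpoints related to retention in care", and adds ART initiation. In Subject Population, the text below Figure 1 has a matching sentence: "For HIV-positive children entering the study who are not currently on ART, we will be able to compare retention in care".
- **All enrolled children.** Expected Results plans to evaluate "loss to follow-up of HIV-positive children (pre-ART and on ART), compared to the current standard of care program". Figure 1 lists retention for the untreated group and also for the treated group: "Receiving ART (endoints: viral suppression/HIV RNA >1,000 c/mL; pattern of retention". The Subject Population paragraph after Table 2 names retention as an outcome of the whole cohort.
- **Children on ART.** The Overview of Study Design describes the evaluation as one of retention and viral suppression in children on ART.

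Secondary objective 3, which ought to settle the matter, concerns "loss to follow-up (not seen in clinical care >3 months) and ART initiation in HIV-positive children not on ART at study entry". The Statistical Analysis Plan section says only that the primary-objective analysis is repeated for this objective with suitable outcomes.

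**The concern.** These statements are incompatible rules, not detail left for later. A SAP author could follow the sampling section, Expected Results or the design overview and claim to comply with the protocol each time. The three choices give very different sample sizes and answer different questions. Allocation is by facility and no masking is described, so an open choice of population could also be made after the data are known.

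The endpoint is not peripheral. Research Goals and Objectives names retention beside viral suppression in the overall aim, and the Summary even places it in the primary objective, although the formal list of objectives puts loss to follow-up among the secondary ones. If the sampling section were followed literally, the retention comparison would rest on a small minority of the cohort and would omit the children on ART, who are most of those enrolled.

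**Working it through.** **Inputs from the protocol**
- Total enrolment 666, 333 per arm (Study sampling procedures).
- Share not on ART at entry: 15% (Study sampling procedures). Subject Population puts 85-90% on ART, so 10-15% are not.
- Planning contrast 80% vs 90% suppression, 5% significance, 80% power, 199 per arm, 444 in total after 10% loss (Table 3 and the text after Table 4).

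**The plan's own figures reproduce**
- Two-proportion formula, two-sided 0.05, 80% power, no continuity correction: n = [1.96·√(2·0.85·0.15) + 0.842·√(0.80·0.20 + 0.90·0.10)]² / 0.10² = 199 per arm.
- 199/0.90 = 221.1, rounded up to 222 per arm, or 444 in total.
- 444 × (1 + 0.20 + 0.15 + 0.15) = 666.

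**Size of the retention set under each reading**

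| Reading | Children | Per arm |
|---|---|---|
| Not on ART at entry | 0.10 × 666 = 67 to 0.15 × 666 = 100 | 33 to 50 |
| On ART | 0.85 × 666 = 566 to 0.90 × 666 = 599 | 283 to 300 |
| All enrolled | 666 | 333 |

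**Precision**

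The protocol gives no arm-specific rates for loss to follow-up. Take 10% in each arm as an assumption. It equals the sample-size allowance, which is not a planning rate for this endpoint. Ignore clustering by facility and family. The 95% half-width for the difference is 1.96·√(2·0.10·0.90/n):
- n = 50: 1.96·√(0.18/50) = 0.118, or 11.8 points.
- n = 333: 1.96·√(0.18/333) = 0.046, or 4.6 points.

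**Illustrative power** (assumed rates, two-sided 0.05, no clustering)

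| Loss, control vs FAM-CARE | 33 per arm | 50 per arm | 333 per arm |
|---|---|---|---|
| 20% vs 10% | 21% | 29% | 95% |
| 15% vs 5% | 27% | 38% | 99% |
| 10% vs 5% | 12% | 16% | 69% |

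Allowing for clustering would widen the intervals and lower the power in every column.

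**Does objective 3 decide it?** No. The qualifier about ART status at entry may attach to ART initiation alone or to loss to follow-up as well. The instruction to repeat the primary analysis does not help: the primary outcome is defined in children on ART, while its intent-to-treat step compares all children at the facilities.

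**The case against.** The strongest reply is that this is loose drafting and that the weight of the text favours all children. Much of that stands.

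- No sentence says that retention is assessed only in untreated children. The restriction is inferred from the paired sentences in Study sampling procedures and the matching sentence below Figure 1.
- Those paired lists are not exhaustive. They give no viral endpoint to children untreated at entry, yet Figure 1 does, and Study Procedures tests their viral load once they start ART.
- The text below Figure 1 goes on to compare retention between children in and outside the FAM-CARE program at FAM-CARE sites, with no ART limit.
- The qualifier in objective 3 fits ART initiation most naturally, and the hypothesis beneath it is unrestricted.
- Loss to follow-up is formally secondary, and the trial is sized on the viral endpoints.

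A reader might also infer more than the documents support:

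- That the trial could not say whether FAM-CARE keeps treated children in care. Table 5 collects attendance and missed visits for all HIV-positive children, and several sections plan that comparison, so no information is lost.
- That the untreated group shrinks as children start ART. It is defined by status at entry, so membership is fixed.
- That joint visits act only on treated children. The FAM-CARE program description admits ART-naïve children and gives the whole family same-day appointments.

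What the reply does not remove is the conflict. The sampling section is where a SAP author would look for analysis populations, and it omits retention for treated children. The design overview points in yet another direction. A later SAP could choose among these readings but could not comply with all of them.

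**Conclusion.** The concern holds as an inconsistency in the analysis population of a secondary endpoint that is also one of the two outcomes in the overall aim. It does not show that the trial will fail to assess retention in treated children. Following the sampling section would leave 33-50 children per arm instead of 333, with a half-width of about 11.8 points at 50 per arm against 4.6. The counts follow from the protocol's own 10-15% and 666. The precision and power figures rest on assumed loss rates and on independence between children, so they illustrate scale and are optimistic. The protocol should be corrected because the choice changes who is analysed and costs nothing to settle now.

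**What to change.** Split secondary objective 3 into two endpoints:

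1. Loss to follow-up/retention over 18 months in all enrolled children, whatever their ART status at entry, with results also shown by ART status at entry.
2. ART initiation in children not on ART at entry.

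Then align the Overview of Study Design, the paragraph below Figure 1 and Study sampling procedures with Expected Results and Figure 1. In the Statistical Analysis Plan section, name the population when the primary analysis is repeated for objective 3.

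The cost is a wording amendment. No new data, visits or participants are needed, because Table 5 already schedules attendance data for every HIV-positive child.

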**ii. Research Protocol/Methods**

1. ***Study Procedures***

After obtaining written informed consent from the caregiver and verbal informed assent from children < 12 years, eligible HIV-positive children will be enrolled in the study into the FAM-CARE or control arm depending on the facility h/she attends. An enrollment visit will be conducted, during which caregivers will be interviewed to collect demographic, medical and HIV-related information about the child. Clinical/laboratory data will be abstracted from clinic medical records. The caregiver will be interviewed regarding HIV infection status of other family members and clinical/treatment history obtained for other HIV-positive family members by interview and chart abstraction. Children will be seen for a study-specific visit at enrollment and every three months by study staff. Study visits will be scheduled to coincide with routine health services visits to the child as much as possible.

At each study visit, the study nurse will obtain interim clinical history (e.g., medical/HIV history and CD4 count and, for children on treatment, ART history, current regimen, and adherence questionnaire) by caregiver interview and abstraction of clinical and laboratory data from medical records and record on study data collection tools. Clinic visit attendance and pharmacy drug pick-up for children receiving ART will be obtained by chart abstraction. Blood will be drawn from the HIV-positive children on ART for study viral load testing at enrollment and at 6, 12, and 18 months on study. HIV-positive children not on ART at enrollment who initiate ART during study follow-up will have viral load testing at ART initiation and every six months during the study. Table 3 shows the proposed schedule of data collection.

Informed consent will be sought from other HIV-positive adult (>18 years) family members for abstraction of data on HIV-related clinical and laboratory from their medical records at enrollment and approximately every 6 months. For HIV-positive adolescents between the ages of 15 through 17 years, informed consent for data abstraction from existing medical records will be obtained from the mother/caregiver. No study visits or procedures are required for HIV-positive adult or adolescent age 15 through 17 year-old family members; only data abstraction will be performed. This consent can be obtained at enrollment or any time during the study. However, this will not be required to enroll a child into the study.

***b) Schedule of Evaluations***

**Table 5** shows the schedule of evaluations.

**Table 5.** Schedule of Evaluations

| **Data Collection** | **Forms** | **Enroll-ment** | **3 mos** | **6 mos** | **9 mos** | **12 mos** | **15 mos** | **18 mos** |
| --- | --- | --- | --- | --- | --- | --- | --- | --- |
| Informed consent caregiver-child | - Caregiver-child informed consent form | X |  |  |  |  |  |  |
| Age-appropriate assent of children > 12 years | - Verbal assent form | X |  |  |  |  |  |  |
| Informed consent for medical record abstraction from HIV-positive family members | - Family member informed consent form | X (or anytime during study) |  |  |  |  |  |  |
| Demographic data | - Enrollment Form | X |  |  |  |  |  |  |
| Family HIV history | - Enrollment Form | X |  |  |  |  |  |  |
| Treatment and viral load data for HIV-positive caregivers interview and medical record abstraction ) | - Enrollment and Follow-up Visit Form - Family Member Clinical record abstraction Form | X | X | X | X | X | X | X |
| Treatment and viral load data for HIV-positive adult family members by interview (and medical record abstraction if consent is obtained) | - Family member clinical record abstraction form | X |  | X |  | X |  | X |
| *All HIV-positive children* | | | | | | | | |
| Demographics (DOB, gender) | - Child Enrollment Form | X |  |  |  |  |  |  |
| HIV history | - Child Enrollment Form | X |  |  |  |  |  |  |
| Interim (between visits) HIV history | - Child Follow-up Form |  | X | X | X | X | X | X |
| CD4 count (program data) | - Child Clinical Record Abstraction Form | X |  | X |  | X |  | X |
| Medical visit attendance timeliness/missed visits | - Child Clinical Record Abstraction Form |  | X | X | X | X | X | X |
| *HIV-positive child receiving ART** | | | | | | | | |
| ART history | - Child Enrollment Form - Child Follow-up Form | X |  |  |  |  |  |  |
| Current ART regimen | - Child Clinical Record Abstraction Form - Child Enrollment and Follow-Up Forms | X | X | X | X | X | X | X |
| Adherence questionnaire | - Child Enrollment Form - Child Follow-up Form | X | X | X | X | X | X | X |
| Pharmacy ART pick-up | - Child Clinical Record Abstraction Form | X (if already on ART) | X | X | X | X | X | X |
| Viral load | - Blood draw | X |  | X |  | X |  | X |

*Collected any time a child is initiated on ART (on ART at entry or starts ART during study)

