However, there is potential correlation of viral outcomes of children from the same family as well as children from the same facility, thereby violating the assumption of independence required for validity of the chi-square test. We propose to use multilevel generalized linear models to account for the potential intra-cluster correlation due to family unit and facility. In addition, we will adjust for potential confounding that may arise due to imbalances in children’s characteristics between study arms.

b) If the FAM-CARE program decline rate is substantial (>10%) and baseline characteristics of children differ significantly between those who accept FAM-CARE and those who decline, we propose to use the propensity score method to match and compare FAM-CARE and non- FAM-CARE participants. Using data from the FAM-CARE sites, we will estimate the probability of accepting FAM-CARE program given the baseline children and family characteristics. Using special matching algorithms, we will develop a statistical control group that will be compared with the FAM-CARE group. Regression modeling will be used to estimate the effect of the FAM-CARE group compared to the control group.

c) Finally, we will perform an intent-to-treat analysis in which all children at facilities offering the FAM-CARE program will be compared to all children at facilities without FAM-CARE program.

To answer primary aim 2, we will use the same statistical approach described for specific aim 1 above.

To answer secondary objectives 1 and 3, the analysis for the primary objective described above will be repeated using the appropriate outcomes.

To identify factors associated with viral suppression and HIV RNA >1,000 copies/mL (secondary objective 2), we propose to use multilevel logistic regression models to estimate the association between viral suppression and putative factors in each study arm. Examples of factors that might be evaluated include age and gender of child, when ART initiated and ART regimen, serious illness or hospitalization, timeliness of pharmacy drug pick-up, school attendance, family size, number of other HIV-positive individuals in family, HIV treatment and clinical status of other HIV-positive family members, disclosure of HIV status within family.

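### Attendance is scheduled for abstraction only from month 3, so the missed-visit, time-out-of-care and loss-to-follow-up comparisons have no pre-programme value to adjust for

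*Protocol*

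**What the plan says.** In Table 5 (Schedule of Evaluations), the row for "Medical visit attendance timeliness/missed visits" reads in full "Medical visit attendance timeliness/missed visits | - Child Clinical Record Abstraction Form | | X | X | X | X | X | X": the enrolment cell is empty and the six follow-up visits are marked. Other rows do carry an enrolment mark, namely CD4 count, viral load, the adherence questionnaire and pharmacy pick-up. CD4 and pharmacy pick-up are recorded on the same Child Clinical Record Abstraction Form. The pick-up entry at enrolment is conditional: "X (if already on ART".

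The Study Procedures text gives the source: "Clinic visit attendance and pharmacy drug pick-up for children receiving ART will be obtained by chart abstraction". It names no period before enrolment.

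Under Expected Results the study will evaluate the programme's effect on "missed visits, time out of care, and loss to follow-up of HIV-positive children (pre-ART and on ART"). Secondary objective 3 covers loss to follow-up, defined as more than 3 months without being seen in clinical care. Retention is also part of the overall aim, and the Summary places it in the primary objective.

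The Statistical Analysis Plan section says the analysis will "adjust for potential confounding that may arise due to imbalances in" children's characteristics between arms, and that secondary objectives 1 and 3 repeat the primary analysis.

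**The concern.** Allocation was by coin toss of four clusters, stratified by hospital or health centre, so each arm has one cluster per stratum. That gives only 2 × 2 = 4 possible allocations, and chance cannot be relied on to balance attendance habits across facilities. The usual partial remedy is to measure the outcome before the programme and adjust for it. The virological endpoints have such a measure in the enrolment viral load, although it too follows the start of the programme. Attendance has none.

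A later SAP cannot repair this, because it cannot adjust for data that were not collected. What is at stake is bias, in either direction, in the retention comparisons, and some lost precision for missed visits and time out of care.

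**Working it through.** **1. Is the blank cell a real scheduling choice?** Set side by side in Table 5:

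| Row | Form | Enrolment | Months 3–18 |
|---|---|---|---|
| CD4 count | Child Clinical Record Abstraction | marked | 6, 12, 18 |
| Pharmacy pick-up | Child Clinical Record Abstraction | marked, if on ART | all |
| Attendance/missed visits | Child Clinical Record Abstraction | blank | all |

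The chart is opened on the same form at enrolment, and attendance is the item not scheduled.

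**2. The plan's own figures.** Table 3 gives 199 per arm for 80% versus 90% (two-sided 5%, 80% power). The standard two-proportion formula with pooled variance returns 199. Dividing by 0.90 for loss to follow-up gives 221.1, rounded up to 222 per arm, or 444 in total. Both reproduce. They concern viral suppression and assume no correlation within facilities. No sample size or power is stated for retention.

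**3. How far could a facility difference mislead?** The Protocol gives no loss rate by arm and no intra-cluster correlation (ICC) for retention, so these are assumptions: loss 10%, no true FAM-CARE effect, 333 children per arm, two equal clusters per arm (m = 166.5). For a test that ignores clustering:

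- Design effect: DEFF = 1 + (m − 1) × ICC
- True error of a nominal 5% test: 2 × [1 − Φ(1.96 / √DEFF)]
- Standard deviation of the chance gap between arms: √(ICC × 0.10 × 0.90)

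| Assumed ICC | DEFF | True error | SD of gap (points) |
|---|---|---|---|
| 0.005 | 1.83 | 15% | 2.1 |
| 0.01 | 2.66 | 23% | 3.0 |
| 0.02 | 4.31 | 35% | 4.2 |
| 0.05 | 9.28 | 52% | 6.7 |

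**4. What would a baseline change?** If a pre-programme covariate correlates ρ with the facility effect, the residual ICC is about ICC × (1 − ρ²). At ICC 0.02:

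| ρ | DEFF = 1 + 165.5 × 0.02 × (1 − ρ²) | True error |
|---|---|---|
| none | 4.31 | 35% |
| 0.5 | 3.48 | 29% |
| 0.8 | 2.19 | 19% |
| 0.9 | 1.63 | 12.5% |

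The error stays above 5% throughout. The contribution of the missing field is the distance between the first row and the later ones, not the whole 35%.

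**5. Precision.** For a missed-visit measure with an assumed child-level pre/post correlation of 0.5, adjustment leaves 1 − 0.5² = 0.75 of the residual variance. That is worth 1/0.75 = 1.33 times as many children at the individual level. It does not add clusters.

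**The case against.** **The root problem is two clusters per arm, not one blank cell.** This stands. Step 4 shows that a baseline only lowers the error. A reader might infer that the missing field is what makes a facility difference indistinguishable from a FAM-CARE effect, and that filling it would separate the two. The documents do not support that.

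**The planned analysis is not the naive test.** This also stands in part. The Protocol says the chi-square needs independence, and proposes multilevel models for family and facility. A reader might take as the price of the missing field that existing losses of 10% versus 5% would be declared significant 69% of the time, or 10% versus 7% 28% of the time (333 per arm). Those figures reproduce, but they assume the gaps and treat children as independent. A multilevel model allows for correlation, but without a prior measure it cannot shift the estimate to correct a prior difference.

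**Pharmacy pick-up already serves as a baseline.** Partly. It covers an estimated 85–90% of children, and the Protocol describes monthly visits and pick-up as going together for children on ART. But it has no stated look-back and omits children not yet on ART, who count towards retention. Once FAM-CARE runs, one member of a stable family may collect for all, so pick-up is no longer the child's own attendance.

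**Loss to follow-up has no true baseline here.** Correct. Entry requires that the child is receiving care at the facility, so children already lost are absent and a look-back understates facility differences in loss.

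**Attendance may in fact be abstracted at enrolment.** Study Procedures describes abstraction at each study visit, and enrolment could be read as one. Table 5 is more specific, and neither place names a pre-programme period. FAM-CARE began before the study, so a value taken just before enrolment could already carry its effect.

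**Conclusion.** The point holds in limited form. Table 5 schedules no attendance value before the programme for any child, so the promised adjustment cannot use one in the missed-visit, time-out-of-care or loss-to-follow-up comparisons. Pharmacy pick-up at enrolment is only a partial substitute. With two clusters per arm, a prior facility difference may be read as a programme effect, and a baseline would reduce this and make it visible without removing it.

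The size is illustrative. Under the working assumptions (ICC 0.02, 10% loss, 333 per arm, unclustered test), the false-positive rate goes from about 35% to between 29% and 12.5%, depending on how well past attendance tracks the facility effect. The ICC, loss rate and correlations are assumed. The gain is clearest for missed visits and time out of care and weaker for loss to follow-up. The two listed primary objectives are virological and are not affected. This is a worthwhile, inexpensive improvement to the retention analyses.

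**What to change.** - **Table 5 and the Child Clinical Record Abstraction Form:** add an enrolment entry to the attendance row. From the existing chart, abstract visits scheduled and visits attended over a fixed calendar window (12 months, for example) ending when FAM-CARE started, with the same window at control facilities. The Protocol should state the programme's start date, which it does not now give.
- **Analysis:** include the child's proportion of visits kept, with an indicator for children not in care at the facility during the window, as a covariate in the missed-visit and time-out-of-care models. Use it as a supportive covariate only for loss to follow-up.
- **Reporting:** show before-to-after attendance by facility beside the arm comparison, and report by arm how many children lack the baseline. State that, with two clusters per arm, adjustment does not fully separate facility from programme.

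**Cost:** extra abstraction time on about 666 charts, by study nurses who already abstract them, with no added visit or blood draw. Newly diagnosed and transferred-in children will have no value. Because FAM-CARE actively tests family members and helps transfer them in, that share may differ between arms, which is why missingness must be reported by arm.
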